### Organization and ethical concerns

2.5

This is a single‐center, investigator‐initiated study. The study protocol has been approved by the local ethics committee. All patients will provide written informed consent before study participation. All investigators will adhere to Good Clinical Practice and to the ethical principles of the Declaration of Helsinki.

An independent Data Safety Monitoring Board (DSMB) consisting of an interventional cardiologist, anesthesiologist and statistician has been established for this study to oversee safety. A blinded interim analysis will be performed after 24 patients have been included and additional interim analysis will be performed when deemed necessary by the DSMB. The DSMB will have access to the unblinded study data (including patient characteristics, invasive procedure details, primary and secondary efficacy endpoints, safety endpoints and relevant serious adverse events) and can give the following recommendations: (i) proceed with the trial according to protocol, (ii) modify the study protocol or study procedures (including, but not limited to, changes in inclusion/exclusion criteria, frequency of safety monitoring, alterations in study procedures and follow‐up period for the purposes of safety), and (iii) terminate inclusion of new patients into the trial.

## RESULTS

3

Study enrollment started on December 21, 2021 and the estimated completion of the primary assessments is June 2025. To date, January 2, 2023, a total of 18 patients have been enrolled in the study. Three patients have completed the 1‐year follow‐up. The baseline characteristics of the patients currently enrolled are shown in Supporting Information: Table 1.

## DISCUSSION

4

The SCRAP trial will be conducted in a large specialized hospital in the Netherlands (Catharina Hospital, Eindhoven). In the Netherlands, the “National Health Care Institute” evaluates certain aspects of our health care system to determine if a treatment modality is effective and should be part of insured health care. In November 2019, the National Health Care Institute evaluated the treatment modality neuromodulation in patients with chronic pain, including patients with RAP. The report concluded that, based on the available literature (June 2018), spinal cord stimulation should not be considered as an effective treatment modality in patients with refractory angina pectoris and should therefore no longer be part of insured health care in the Netherlands.^21^ An important note in the report was the lack of randomized controlled trials in patients with RAP and spinal cord stimulation. However previous results from our center show that spinal cord stimulation leads to significantly improved quality of life with significant reduction in angina pectoris episodes and less use of short‐acting nitrates.^13^ Additionally in the ESC guideline “chronic coronary syndromes” varying levels of evidence with regard to treatment options for patients with RAP have been described.^15^ The guideline recommendation for use of SCS in RAP is Class IIB; level of evidence B—may be considered. With the conclusion that additional research is necessary to determine the exact role of the various treatment modalities for RAP. Taking all the afore mentioned points together it can be concluded that the strength of the studies performed up to date has been insufficient to definitively show a positive effect of SCS in patients with RAP. And with the report of the National Health Care Institute it is currently not possible for treating cardiologists in the Netherlands to refer patients with RAP to specialized centers, such as the Catharina Hospital, for SCS treatment, emphasizing the urgent need for studies such as the SCRAP trial to clarify the role of SCS in patients with RAP.

The decision to use changes in myocardial ischemia, measured with myocardial perfusion PET scanning, as primary endpoint is based on the afore mentioned report of the National Health Care Institute. An important comment in the report was that evidence of reduction in myocardial ischemia is currently missing, which led to the formulation of the chosen primary endpoint.^21^ Taking into consideration the importance of patient related outcome measures (PROMs) key secondary endpoints are PROM outcomes.

The choice of 6 months SCS treatment is based on previous research that has shown that changes can be seen in myocardial blood flow (using PET) after 3–6 weeks of SCS therapy.^22^, ^23^ Whilst also taking into consideration that changes in myocardial ischemia (using MIBI) were not yet seen after 3 months of SCS therapy in the study by Diedrichs et al.^14^

An important concern voiced in previous literature is the risk of adverse events related to the spinal cord stimulator implantation in general. Adverse events range from lead dislocation to device related infections with a reported incidence of up to 40%.^3^, ^24^ Spinal cord stimulation is used in a variety of chronic pain syndromes such as RAP and failed back surgery syndrome (FBSS). One review reported on adverse events specifically related to patients with RAP and SCS. This review described 1% of patients with an infection (1 out of 104 patients) and 7.8% of patients with lead migration or fracture (10 out of 128 patients).^25^ As is true for all interventional therapies operator experience will lead to a reduction of the number of adverse events over time. Our center has been implanting spinal cord stimulators for the indication RAP since 2009 and a recent observational study carried out in our center showed a low percentage of adverse events over a follow‐up period of one year (2.3%; 2 out of 87 patients),^13^ showing that the risk of adverse events is low in patients with RAP receiving a spinal cord stimulator. The risk of a complication related to the spinal cord stimulator implantation has been taken into consideration in the design of the SCRAP trial in two ways. First, the drop‐out rate of 10% was imbedded into the sample size calculation and secondly in the SCRAP trial adverse events related to the spinal cord stimulator implantation have been added as safety end points (Table 3) and will be reported at the end of the study period.

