Proven ischemia: ○ MIBI‐SPECT: SSS of at least 1, in combination with SDS of at least 1 (1–4 mildischemia, >4 moderate to severe ischemia). ○ Fractional flow reserve: <0.80, with no intervention options (determined by interventional cardiologist). ○ MRI perfusion: ≥1 segment of subendocardial hypoperfusion during stress perfusion, not present at rest and no matching fibrosis (using 16 segment AHA heart model). ○ Myocardial perfusion PET: Semi‐quantitative measurement: SSS of at least 1, in combination with SDS of at least 1 (1–4 mild ischemia, >4 moderate to severe ischemia). Quantitative measurement: reduced myocardial perfusion reserve.
No revascularization (PCI and/or CABG) performed between ischemia testing and study inclusion.
Age >18 years.

Abbreviations: CABG, coronary artery bypass grafting; CAG, coronary angiogram; MIBI‐SPECT, methoxyisobutylisonitrile single photon emission computed tomography; MRI, magnetic resonance imaging; PCI, percutaneous coronary intervention; PET, positron emission tomography; SDS, summed difference score; SSS, summed stress score.

**Table 2 clc24016-tbl-0002:** Exclusion criteria.

Acute coronary syndrome during the 3‐month period before screening.
Life expectancy less than 12 months.
Inability to perform a 6‐min walking test.
Inability to give informed consent.
No proven ischemia (see Table 1 Inclusion criteria).
Spinal cord disease which could prevent correct positioning of the lead in the epidural space; to be determined by the anesthesiologist performing the implantation.
Anticoagulation therapy that cannot be stopped/bridged before spinal cord stimulator implantation.
Inadequate paresthesia coverage, during implantation, of the thoracic region where angina complaints are localized.
Pregnancy.
Mild Cognitive Impairment or dementia.
Concomitant symptomatic valvular heart disease including severe aortic stenosis and/or regurgitation, severe mitral valve stenosis and/or regurgitation or severe tricuspid valve regurgitation.

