#### Secondary endpoint objectives

2.2.2

An overview of the secondary objectives is given in Table 3. The secondary objectives are patient related outcome measures (PROMs), major adverse cardiac events (MACE) and safety endpoints. MACE consists of the following components; (i) number of hospital admissions due to an acute coronary syndrome (ACS), (ii) undergoing revascularization (PCI and/or CABG), (iii) number of presentations at the emergency room due to angina pectoris and, (iv) cardiovascular mortality. ACS is defined in accordance with the universal definition of myocardial infarction as a high‐sensitivity troponin T with at least one value above the 99th percentile of the upper reference limit with at least one of the following; (1) symptoms of myocardial ischemia, (2) new ischemic electrocardiographic changes, (3) development of pathological Q waves, (4) imaging evidence of loss of viable myocardium or new regional wall motion abnormality or, (5) intracoronary thrombus detected on angiography or autopsy.^17^ The clinical endpoints will be investigator reported. The Seattle Angina questionnaire (SAQ; Appendix 3), RAND 36‐item Health Survey (RAND‐36; Appendix 4) questionnaire, Numeric Rating Scale (NRS‐scale; Appendix 5), CCS class, 6‐min walking test (6‐MWT), and review of patient files will be used to obtain the secondary objectives (Table 3).

**Table 3 clc24016-tbl-0003:** Secondary objectives.

Changes in absolute quantification of myocardial blood flow using myocardial perfusion PET scan including myocardial blood flow & myocardial flow reserve regionally and globally.
Patient related outcome measures: ○ Patient condition using 6‐minute walking test; ○ Frequency of angina pectoris using the SAQ; ○ Severity of angina pectoris using the Numeric Rating Scale; ○ Grading of angina pectoris using the Canadian Cardiovascular Society class; ○ Quality of life using the RAND 36‐item Health Survey; ○ Frequency of short‐acting nitrate use using the SAQ.
Major Adverse Cardiac Events: ○ Number of hospital admissions due to acute coronary syndrome; ○ Revascularization (CABG and/or PCI); ○ Number of presentations at the emergency room due to angina pectoris; ○ Cardiovascular mortality.
Safety endpoints; ○ Number of device infections (lead and/or battery); ○ Number of device dislocations (lead and/or battery); ○ Number of lead fractures/breakages; ○ Number of lead failures; ○ Number of battery end of life.

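### The Discussion presents the Table 3 safety endpoints as covering implantation-related adverse events, but no item in Table 3 covers harm from the implantation procedure itself

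*Protocol article*

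**What the plan says.** The Discussion calls the risk of implantation adverse events an important concern and says that the design deals with it in two ways. The first is the 10% drop-out allowance. The second is that "adverse events related to the spinal cord stimulator implantation have been added as safety end points (Table 3"), with reporting planned for when the study closes.

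Table 3 (section 2.2.2) is the list referred to. Its safety items are "Number of device infections (lead and/or battery"), then "Number of device dislocations (lead and/or battery"), then "Number of lead fractures/breakages", then "Number of lead failures", and finally a count of batteries reaching end of life. There is no open item for other events.

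Three other places bear on the point:

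- Section 2.1.2 describes the operation: propofol and remifentanil sedation, a Tuohy needle into the epidural space at Th7–8, and a lead advanced to C7–Th1.
- Table 2 excludes patients with "Anticoagulation therapy that cannot be stopped/bridged before spinal cord stimulator implantation", so patients whose anticoagulation can be interrupted or bridged may enter.
- Section 2.5 gives the DSMB access to data that include "safety endpoints and relevant serious adverse events", naming the two separately.

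**The concern.** The Discussion sentence is about harm related to the implantation. The table it cites counts what happens to the device, plus infection. A reader of the final report who relies on that sentence would take the Table 3 counts as the account of implantation harm, although harm from the needle, the sedation or the interruption of anticoagulation has no line there.

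This matters because every participant is implanted, including for a six-month period without stimulation. The Discussion also argues, from 2 events in 87 patients at the same centre, that the risk is low. The trial's safety endpoints will be read as the test of that statement.

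**Working it through.** The point rests on comparing sections of the article. Arithmetic serves only to give a sense of scale.

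**1. Which events have an endpoint?**

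| Event arising from the plan's own procedure | Source | Safety item in Table 3 |
|---|---|---|
| Infection of lead or battery | 2.1.2 | Yes |
| Dislocation of lead or battery | 2.1.2 | Yes |
| Fracture or failure of the lead | 2.1.2 | Yes |
| Dural puncture, epidural bleeding, neurological injury | 2.1.2, epidural access | None |
| Sedation event | 2.1.2, sedation | None |
| Bleeding or thrombotic event linked to interrupted anticoagulation | Table 2 | None |
| Re-operation for a reason outside the five items | 2.1.2 | None |

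The fifth item, battery end of life, is not a consequence of the operation. None of the five names an operative or neurological injury.

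**2. Does another endpoint cover them?** The MACE components (section 2.2.2) are admissions for acute coronary syndrome, revascularization, emergency presentations for angina, and cardiovascular death. A non-fatal procedural injury is none of these.

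**3. Does the follow-up section widen the list?** Section 2.3 asks patients to report stimulator complications, but specifies them after an i.e. as infection, battery or lead dislocation, and lead fracture. That is again the device list.

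**4. Who is counted?** Table 2 makes inadequate paresthesia coverage found during implantation an exclusion. By section 2.1.2, coverage is tested after the needle and lead are in the epidural space and sedation has been given. The Figure 2 legend places implantation before randomization. These patients have been exposed to the procedural risk, but a count restricted to randomized patients would omit them.

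**5. Scale.** Inputs: 72 patients to be included (section 2.4) and 2 of 87 with an adverse event at the centre (Discussion).

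- The planned number reproduces. A paired two-sided t test with difference 2.5, SD 7, α 0.05 and power 0.80 needs n = 64 (power 0.803), and 64 / 0.9 = 71.1, rounded up to 72. The safety list plays no part in this.
- Centre rate: 2/87 = 2.3%.
- One affected patient among 72 implants: 1/72 = 1.4 percentage points.
- The documents give no rate of procedural injury. If it were between 0.5% and 3% per patient (an assumption), the expected number would be 72 × 0.005 = 0.36 to 72 × 0.03 = 2.16. The chance of at least one would be 1 − 0.995^72 = 30% to 1 − 0.97^72 = 89%.

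**The case against.** The strongest reply is that the Discussion paragraph shows what it means by implantation adverse events. It describes them as ranging from lead dislocation to device infection, then cites 1 infection in 104 patients (1.0%) and lead migration or fracture in 10 of 128 (7.8%). Table 3 and the list in section 2.3 have broadly the same scope. Read that way, the sentence is loosely worded but does not contradict the table. This stands, and it is why the point is a scope mismatch.

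A second reply is that the article does not show harm going unrecorded. The DSMB sees relevant serious adverse events, and the investigators are bound to Good Clinical Practice. Patients are asked to report emergency visits and admissions, there is ward monitoring and a one-week wound check, and general adverse-event recording is commonly left to the full protocol. This also stands. It concerns collection, however. The Discussion makes a positive statement about what the reported endpoints contain, and an event seen by the DSMB or found at a visit does not thereby become one of them.

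Two stronger readings are tempting and are not supported:

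- A reader might infer that the trial will publish a complication rate that is too low. Table 3 plans separate counts and defines no pooled rate, and the definition behind the earlier 2.3% is not shown.
- A reader might infer that a broken lead will be counted twice, as a fracture and as a failure. The article does not say that failure includes fracture, and a boundary between two adjacent items is detail that the full protocol may give.

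**Conclusion.** The point holds as a mismatch between the Discussion and Table 3. The Discussion presents the safety endpoints as covering adverse events related to the implantation. The listed endpoints cover device events and infection, and leave out harm from epidural access, sedation and interrupted anticoagulation. As written, the reported endpoint set would understate implantation harm if such events occur, including in patients excluded during the operation.

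The size cannot be fixed from the documents. The figure of 1.4 percentage points per patient is an illustration, and it assumes that the 72 planned patients are the 72 implants. Nothing here changes the primary endpoint, the comparison of stimulation with no stimulation, or the sample size. Nor does it follow that serious harm goes uncollected.

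**What to change.** Add one safety item to Table 3: *any other adverse event related to the device or the implantation procedure, including re-operation*. Report it as number of patients and number of events, with all patients in whom implantation was started as the denominator. State that this includes patients excluded during implantation for inadequate paresthesia coverage.

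Narrowing the Discussion sentence to device-related events would also remove the mismatch, but would leave procedural harm without an endpoint. Widening the table delivers what the sentence promises.

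The cost is one table row and one line on the case report form. Review of patient files is already a planned source for the secondary objectives, so patients enrolled before the change can be covered. The downside is that the reported figure may be somewhat higher and less comparable with the centre's earlier 2.3% (2/87). Reporting the five existing items separately, as now planned, preserves what comparison there is.

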## LIMITATIONS

5

There are a number of limitations with regard to the SCRAP trial. One limitation is the difference in myocardial ischemia on which the sample size calculation is based. The power of the study is based on a relative reduction in myocardial ischemia of 25% after treatment with SCS, in absolute numbers a reduction from 10% to 7.5% of myocardial ischemia. Whilst this is a relatively modest difference, it is deemed clinically relevant. Patients with more than 10% myocardial ischemia have a worse prognosis in comparison to patients with less than 10% myocardial ischemia,^15^ making the chosen difference clinically relevant. A second limitation of the study is the single‐center design and the reason for this choice is twofold. Firstly the number of patients meeting the selection criteria is expected to be low. Second, the implantation of spinal cord stimulators should be limited to specialized centers to reduce the risk of device‐related complications and the chosen center for the SCRAP trial is such a specialized center.^26^, ^27^

## CONCLUSION

6

The SCRAP trial is an investigator‐initiated, single‐center, double‐blind, placebo‐controlled, cross‐over randomized controlled trial evaluating the efficacy of spinal cord stimulation on the amount of myocardial ischemia in patients with refractory angina pectoris.

## Data Availability

The data that support the findings of this study are available from the corresponding author, [name], upon reasonable request.
